**Fig. 2 Fig2:**

Intra-oral photographs

#### Professionals’ attitude toward working with the guideline

To evaluate the attitudes of professionals working with the CPG, these orthodontists will be asked to complete a questionnaire. The main investigator will personally hand the questionnaire to these practitioners during the outreach visit, after providing all information regarding use of the CPG. The same procedure will be repeated at the end of the trial. If a practitioner fails to respond, a reminder will be sent after 2 weeks.

#### Patients’ experience with preventive strategies

Patients will be asked to complete a questionnaire asking their opinion about the preventive strategies used by their practice. The questionnaire will be sent to all included patients at 6 months after inclusion of the first patients. At that point, the first and last included patients will have undergone approximately 6 and 4 months of treatment, respectively. Two weeks after the questionnaire is mailed, a reminder will be sent.

#### Compliance with working with the guideline

Orthodontists in the intervention group will use the CDSS integrated in the EPF. At each check-up visit, the computer will ask the orthodontist to register the patient’s oral health status and oral hygiene status. Subsequently, the program will generate the preventive measures to be applied following the recommendations of the CPG. This information will then be automatically stored in the EPF. In the control arm of the study, only oral health and hygiene status at the start of treatment will be registered.

### Informed consent

Before starting treatment, all patients in both the intervention and control practices will receive a general letter containing information about the study. Patients will be informed that if they participate, they will be asked to complete a questionnaire, and information regarding oral health and oral hygiene will be extracted from their patient files. Patients at the intervention practices will be given specific information regarding the use of the CPG as part of an informed consent letter that will be signed by the patient and their parents prior to orthodontic treatment. Patients at the control practices will be receiving usual preventative care and will not be asked to give informed consent for the preventive measures used.

### Statistical analysis

#### Reliability of WSL recording

Kappa values will be calculated to evaluate the inter-rater agreement for recording WSLs from intra-oral photographs. For this purpose, ten pre- and post-treatment photographs per orthodontic practice will be analyzed independently by two experienced orthodontists.

#### Primary outcome

To account for the data clustering (in orthodontic practices), a multilevel logistic regression analysis will be applied on patient data, using the presence of new WSLs at T2 (yes/no) as the outcome, and the type of intervention (CPG or usual preventive measures) as the predictor. In this model, the regression coefficient of the predictor “intervention versus control” indicates the effectiveness of the intervention. Given the expected distribution of outcomes, we anticipate the use of binomial logistic regression with a logit link function. We will also examine the influences of age at start of treatment, gender, patients’ opinion on preventive measures, patients’ initial oral health status, patients’ initial oral hygiene status, and patients’ initial sugar intake on the primary outcome measure, by including these factors one by one as predictors in the regression model. These covariates are known to potentially influence the development of WSLs during orthodontic treatment [3, 9]. We do not anticipate a high number of missing values. However, in the event that we do have high numbers of missing values, we will apply a multiple imputation method prior to the planned analyses.

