## Methods/design

### Study design

We have designed a hybrid type 1 effectiveness-implementation study to primarily focus on assessing the guideline’s clinical effectiveness, while simultaneously collecting some preliminary information regarding implementation of the guideline into routine practice. The primary aim of this approach is to examine the effects of the clinical intervention (CPG) on relevant outcomes (the proportion of patients with new or enlarged WSLs), while an additional aim is to obtain preliminary outcomes on the process of CPG implementation [11].

Practitioners will be divided into two groups using cluster randomization at the level of the orthodontic practices. Patients recruited by orthodontists in the intervention group will be treated following the CPG (see intervention section), while patients recruited by orthodontists in the control arm will be treated using standard preventive measures. The proportions of patients showing newly developed or enlarged WSLs will be compared between treatment groups after 6–9 months of treatment with fixed appliances, as well as after completion of orthodontic treatment and removal of the fixed appliances.

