### Primary hypothesis

The trial will evaluate the hypothesis that the preventive measures recommended by the CPG will outperform standard preventive measures with regard to the primary outcome—which is the proportion of patients with newly developed or enlarged WSLs after 6–9 months of treatment, and at the completion of treatment with fixed orthodontic appliances, with an effect size of 0.4.

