#### Sample size and power calculation

We have calculated the number of patients needed to detect a difference in the proportions of patients with newly developed or enlarged WSLs between the intervention group using the CPG and the control group using standard preventive strategies. Earlier studies show that more than 1 in 4 orthodontic patients develop at least one new WSL during the course of orthodontic treatment [3]. Assuming a power of 80 %, a significance level of 5 %, and an ICC of 0.05 to correct for clustering, we calculated that we must include a minimum of 14 orthodontic practices with 50 patients per practice to detect a medium effect size of 0.4 for reduction in newly developed WSLs. The effect size was arbitrarily chosen, as no previous data establish what would constitute a clinically relevant change. The study is powered to detect an effect of 15 % absolute reduction in prevalence of WLS, under the assumptions specified above. Assuming a drop-out rate of 20 %, we plan to recruit a total of 60 patients per participating practice, resulting in a total inclusion of 840 patients. In a regular orthodontic practice, about 40 patients receive full fixed appliances each month. To account for an overestimation of the number of patients to potentially be included in the practices, we will have a 2-month inclusion period.

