### Outcome parameters

#### Primary outcome

The primary outcome measure is the proportion of patients treated with full fixed orthodontic appliances who develop at least one new or enlarged WSL after 6–9 months of treatment with fixed appliances, and at the completion of treatment, when using the CPG for WSL prevention as compared to usual preventive measures.

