### Measurements

#### Primary outcome

The number of WSLs per patient will be determined by examination of maxillary incisors and canines, mandibular canines, and maxillary and mandibular premolars by two independent observers, who will be blinded to the patient’s intervention status. Standardized pre-treatment intra-oral photographs (T0) will be compared with intra-oral photographs taken after 6–9 months of treatment (T1), and after completion of treatment with fixed orthodontic appliances (T2). If comparison of the T0 photographs to the T1 and T2 photographs reveals an identical white spot on all three images, it will be considered a developmental white spot and will not be counted as a WSL. For each patient, the total number of new and enlarged WSLs will be registered. The proportion of patients showing new or enlarged WSLs will be determined for each group.

A pilot study using pre-and post-treatment intra-oral pictures of 150 patients from three orthodontic practices (50 patients per practice) demonstrated an inter-observer agreement of 0.6, which is considered acceptable. However, this agreement varied among the practices, mainly due to the quality of the intra-oral photographs. In the retrospective pilot study, the photographic technique was not standardized in terms of lighting and camera positioning. For the presently described prospective trial, lighting and camera positioning will be standardized, which will likely lead to better agreement. An earlier *in vitro* study measured artificially induced WSLs on extracted maxillary incisors that were photographed at different angles using standardized techniques. Their results showed non-significant interobserver differences in the surface measurements of WSLs of less than 0.1 mm [13].

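### The primary model tests new lesions at end of treatment only, although the primary outcome is defined as new or enlarged lesions at both 6–9 months and end of treatment

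*Protocol article*

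**What the plan says.** Outcome parameters, Primary outcome, counts patients who "develop at least one new or enlarged WSL after 6–9 months of treatment with fixed appliances, and at the completion of treatment". The Primary hypothesis is framed the same way, as the proportion with "newly developed or enlarged WSLs after 6–9 months of treatment, and at the completion of treatment with fixed orthodontic appliances". The abstract agrees, and Study design adds that the proportions "will be compared between treatment groups after 6–9 months of treatment with fixed appliances, as well as after completion of orthodontic treatment". Measurements, Primary outcome, provides the data for this definition: "For each patient, the total number of new and enlarged WSLs will be registered".

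Statistical analysis, Primary outcome, specifies one multilevel logistic regression, "using the presence of new WSLs at T2 (yes/no) as the outcome", and takes the intervention coefficient from that model as the measure of effectiveness. Neither enlarged lesions nor T1 appears there.

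Sample size and power calculation is mixed. It opens with new or enlarged lesions, but its control rate is for patients who "develop at least one new WSL during the course of orthodontic treatment", and its effect size of 0.4 is for a reduction in newly developed lesions. It uses one 5 % level and does not say which time point that level belongs to.

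**The concern.** The defined endpoint and the modelled endpoint differ in two ways.

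- **Lesion type.** New and enlarged are named as separate categories in the abstract, design, hypothesis, outcome and measurement sections. The model names only new. Patients with enlargement alone change status between definition and analysis.
- **Time point.** T1 is a declared part of the primary outcome, but the primary model never uses it. No section says whether T2 alone decides, whether either time point is enough, or whether both must succeed.

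At stake is which result will count as the primary one. With two event definitions and three ways of combining the time points left open, the choice could be made after the data are seen. The article fixes a specific binary outcome in its analysis section, so this is a contradiction in the text and not a detail left to an analysis plan.

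**Working it through.** **1. The definitions side by side**

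| Section | Lesion type | Time point |
|---|---|---|
| Abstract, Study design, Primary hypothesis, Outcome parameters | new or enlarged | T1 and T2 |
| Measurements | new and enlarged registered | photographs at T0, T1, T2 |
| Sample size, opening sentence | new or enlarged | not stated |
| Sample size, control rate and effect size | new | course of treatment |
| Statistical analysis | new | T2 |

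A patient with one enlarged lesion and no new one at T2 is an event in the first row and a non-event in the last.

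**2. Reproducing the stated sample size**

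Inputs from the sample size section: effect size 0.4, 5 % level, 80 % power, ICC 0.05, 50 patients per practice, 15-point absolute reduction, control rate about 25 %. Assumed: a two-sided test, 7 practices per arm, and 25 % versus 10 %.

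- n per arm before clustering = 2 × (1.96 + 0.84)² / 0.4² ≈ 98.1, rounded up to 99.
- Design effect = 1 + (50 − 1) × 0.05 = 3.45.
- 99 × 3.45 = 341.6 per arm; 341.6 / 50 = 6.83, so 7 per arm and 14 practices in total. This matches the article.
- Cross-check with 25 % versus 10 %: 100 per arm; 100 × 3.45 = 345; 345 / 50 = 6.9, again 7 per arm. The arcsine effect size for these rates is 0.404.
- Effective n per arm = 350 / 3.45 = 101.4. Power for 25 % versus 10 % is 80.8 % (normal approximation for two proportions), or about 82 % on the arcsine scale.

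The stated size therefore fits one test at 5 %.

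**3. What each reading of the two time points implies**

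- *T2 only, as the analysis section says.* One test: type I error 5 %, power about 81 %.
- *Either time point suffices, each tested at 5 %.* Family-wise error = 1 − P(|Z1| < 1.96 and |Z2| < 1.96), with (Z1, Z2) bivariate normal:

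| Assumed correlation | 0 | 0.3 | 0.5 | 0.7 | 0.8 | 0.9 |
|---|---|---|---|---|---|---|
| Family-wise error, % | 9.75 | 9.5 | 9.1 | 8.3 | 7.8 | 7.0 |

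The higher correlations are plausible, because T1 and T2 are scored on the same patients against the same T0 photographs.

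- *Both time points must succeed.* Type I error stays at or below 5 %. With power 0.808 at each time point, joint power is 0.808² ≈ 0.65 at correlation 0, 0.70 at 0.5 and 0.74 at 0.8. This assumes 25 % versus 10 % at T1 as well as at T2.

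**4. Effect of the lesion definition on power**

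The 25 % rate and the effect size of 0.4 are stated for new lesions. A new-only model at T2 therefore matches the planning assumptions and keeps about 81–82 % power. Adding enlarged lesions can only leave each arm's event rate unchanged or raise it. For illustration, put 5 points of enlarged-only patients on top in controls and assume the same relative reduction: 30 % versus 12 %, arcsine effect size about 0.45, power about 90 %. The 5 points and the equal relative reduction are assumptions; the article gives no figure for enlarged-only patients.

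**The case against.** The strongest reply is that the analysis section is clear and safe: one model, one time point, one coefficient, one 5 % test. New may also be shorthand there for new or enlarged, since the sample size section moves between the two terms, and the measurement section says the proportion with new or enlarged lesions will be determined in each group.

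Much of this stands. A reader might infer from the two named time points that the 5 % level is not protected. The article does not support that. Inflation needs a second 5 % test at T1 and a rule that either result suffices, and no section states either. The time points are joined by 'and', which can equally mean that both are required; that costs power, not type I error.

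A reader might also infer a loss of power by taking enlarged-only patients out of the 25 %. For example, 20 % versus 8 % would take power from 82 % to 71 %. That misreads the sample size section, whose rate is already for new lesions, so there is nothing to subtract.

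The shorthand defence does not remove the point. Even if new meant new or enlarged, T1 would still be part of the declared primary outcome and absent from the primary model. The event that is coded should not depend on a guess about wording.

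**Conclusion.** The contradiction is real, in lesion type and in time point, and should be corrected. It concerns what is tested as the primary outcome. It does not show that the planned test exceeds 5 % or that the trial is underpowered: the T2 test as written keeps 5 %, with about 81 % power on the article's own assumptions (two-sided test, equal allocation, 25 % versus 10 %, normal approximation).

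The error range of 7.0–9.75 % and the joint power of 65–74 % are conditional. They describe the either-suffices and both-required readings that the wording leaves open, and they rest on assumed correlations. How many patients would change status through enlargement alone cannot be worked out from the article.

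**What to change.** - **Statistical analysis, Primary outcome:** change the model outcome to at least one new or enlarged WSL at T2 versus T0 (yes/no). Report new-only lesions as a sensitivity analysis.
- **Abstract, Study design, Primary hypothesis and Outcome parameters:** name T2 as the single primary time point. Make T1 secondary, or test it only after T2 is significant. T2 is already the time point of the model and fits the whole-treatment rate behind the sample size.
- **Sample size and power calculation:** state that the 25 % control rate and the effect size of 0.4 come from new lesions and are assumed to apply to new or enlarged lesions.

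The cost is wording. Enlarged lesions are already registered and the T1 photographs are already planned, so no new data are needed. With one primary test and the planning assumptions carried over, the sample size stays as it is. By contrast, splitting the level to 2.5 % at each time point would lower power per test to about 72 %; restoring 80 % would take 121 × 3.45 ≈ 418 patients per arm, or 9 practices per arm. Trial status reports eight practices still to be recruited, so at that stage the choice could be made before outcomes are seen.

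### The effect is read from a valid but unadjusted model and prognostic factors enter only one by one, which leaves a 14-practice comparison exposed to chance baseline imbalance

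*Protocol article*

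**What the plan says.** Under Statistical analysis, Primary outcome, the article specifies a multilevel logistic regression of new WSLs at T2 (yes/no), with type of intervention as the predictor. It says that in this model "the regression coefficient of the predictor “intervention versus control” indicates the effectiveness of the intervention".

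Six further factors are then examined for their influence "on the primary outcome measure, by including these factors one by one as predictors in the regression model": age at start, gender, patients' opinion on preventive measures, and initial oral health, oral hygiene and sugar intake. The article calls them known potential influences on WSL development. No model with several of them together is named as the source of the effect.

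The T0 photograph is not on that list. Under Measurements, Primary outcome, it serves as the reference against which two observers, blinded to arm, compare the T1 and T2 photographs.

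Under Randomization, practices are allocated by software. No stratification, matching or other balancing is described.

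**The concern.** Randomising 14 units gives weaker balance than randomising 840 patients. If the arms differ by chance in something that predicts new lesions, an arm-only estimate carries that difference with it. The plan collects baseline information that could absorb it but keeps that information out of the model that supplies the answer.

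One-by-one entry does not repair this. Each such model deals with at most one imbalance, and the set yields several adjusted arm coefficients beside the designated unadjusted one. The list also mixes kinds of variable. Table 3 puts allocation in month 3 and the patient questionnaire in months 10–12, so patients' opinion follows allocation and may itself be affected by arm. An arm coefficient adjusted for it is not an estimate of the intervention's whole effect.

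**Working it through.** **1. The plan's own figure.** Sample size and power calculation gives "Assuming a power of 80 %, a significance level of 5 %, and an ICC of 0.05 to correct for clustering", and "a minimum of 14 orthodontic practices with 50 patients per practice to detect a medium effect size of 0.4". It also states a 15-point absolute reduction. With a control rate of about 25% (from its more than 1 in 4), this is 25% v 10%.

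- Cohen's h = 2·asin(√0.25) − 2·asin(√0.10) = 0.404, which matches the stated 0.4.
- Design effect = 1 + (50 − 1)·0.05 = 3.45.
- Two proportions, two-sided 5%, 80% power: 100 per arm. Then 2·100·3.45 = 690 patients, and 690/50 = 13.8, so 14 practices.
- Power with 350/3.45 = 101.4 effective patients per arm is 80.8%.

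The stated size therefore reproduces from an unadjusted comparison and does not depend on covariates.

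**2. Size of chance imbalance.** Taken from the article: 14 practices, and 60 recruited per practice with 20% drop-out, which leaves 48. Assumed: 7 practices per arm, and the prevalence p and ICC of the baseline characteristic, which the article does not give.

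SD of the between-arm difference = √[2·p(1 − p)·(ICC + (1 − ICC)/48)/7].

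For p = 0.25 and ICC = 0.05: √[2·0.25·0.75·(0.05 + 0.95/48)/7] = √0.00374 = 0.061. A gap above 10 points is then 0.10/0.061 = 1.64 SD, so it occurs in about 10% of trials. Over a range of ICC at p = 0.25:

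| ICC | SD (points) | Chance of a gap above 10 points |
|---|---|---|
| 0.01 | 4.1 | 1.4% |
| 0.05 | 6.1 | 10% |
| 0.10 | 8.0 | 21% |

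**3. What such a gap does to the result.** Assume a T0 characteristic with 30% prevalence, an overall event rate of 25%, and an odds ratio for new WSL of 2, 4 or 8. Solving 0.7·p0 + 0.3·p1 = 0.25 gives event risks without and with the characteristic of 20.9% and 34.6%, 16.7% and 44.4%, or 12.7% and 53.7%. A 10-point gap then moves the between-arm difference by 0.10·(p1 − p0), which is 1.4, 2.8 or 4.1 points, against a 15-point target.

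**4. What adjustment gains in the planned type of model.** A random-intercept logistic model was simulated with 7 v 7 practices of 50, 25% v 10%, and an outcome ICC of about 0.05. The binary T0 score had 30% prevalence and varied between practices (SD 0.5 on the logit scale). There were 600 runs per setting, with a t critical value on 12 df. Only T0 was added, not age or gender.

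| T0 odds ratio (assumed) | Power: arm only | Power: with T0 | Median SE: arm only | Median SE: with T0 | Correlation of estimate with T0 gap: arm only | With T0 |
|---|---|---|---|---|---|---|
| 2 | 82.2% | 82.5% | 0.352 | 0.354 | 0.13 | 0.00 |
| 4 | 87.5% | 89.2% | 0.343 | 0.359 | 0.24 | −0.02 |
| 8 | 87.8% | 91.8% | 0.335 | 0.367 | 0.37 | −0.03 |

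Power rises by 0.3, 1.7 and 4.0 points. The standard error does not fall. The conditional estimate moves away from zero instead (mean log odds ratio −1.127 to −1.146, −1.180 to −1.249, −1.179 to −1.363). The dependence on the T0 gap disappears. The SD of that gap was about 6.5 points, in line with step 2.

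With no true effect, both models rejected in roughly 6% to 8% of runs. Each power figure has a Monte Carlo standard error of about √(0.85·0.15/600) = 1.5 points. The table is therefore best read as a comparison of two models fitted to the same data sets, not as absolute power.

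**The case against.** The best defence is that nothing here is wrong in the strict sense. An unadjusted multilevel model is valid under cluster randomisation, the article says which coefficient is the answer, and the sample size holds without covariates. All of this stands. A reader might infer that the result is biased or that no estimate is designated; the text supports neither.

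Other stronger readings also fail.

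- *Precision is lost.* For a logistic coefficient the simulation shows no fall in the standard error. The gain is in power, and it is small.
- *Adjustment would add 11 points of power.* A linear variance-reduction formula goes from 74.7% to 85.7% if T0 and outcome correlate at 0.5 both between and within practices. With 25% T0 prevalence and a 17.5% average event rate, 0.5 corresponds to an odds ratio of about 14.5. Nothing in the article suggests that strength.
- *Baseline WSL status is wholly absent.* Initial oral health status is on the list. The Implementation program section describes oral health as including WSLs, and the control arm registers it at the start. It is, however, clinician-rated after practices are allocated, and instruction in rating it is described only for the intervention arm.
- *A T0 lesion opens a second route to the endpoint through enlargement.* That fits the definition under Outcome parameters ("who develop at least one new or enlarged WSL after 6–9 months of treatment with fixed appliances"). The model under Statistical analysis uses new WSLs, for which enlargement gives no extra route.

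Two cautions also stand. One-by-one entry could mean cumulative entry, although even then no adjusted model is named as the source of the effect. And the article is a condensed text: balancing could be described in the full protocol, in which case the imbalance in step 2 would be smaller.

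Finally, a T0 covariate needs care. A spot identical on the T0, T1 and T2 images is reclassified as developmental. If that rule shaped T0 status, the covariate would depend on post-allocation images and partly on the outcome.

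**Conclusion.** The point holds as a weakness in robustness, not as an error. The designated estimate is valid but unprotected against chance imbalance between two small groups of practices, and the one-by-one models do not supply that protection.

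The imbalance has an SD of about 6 points under the assumed 25% prevalence and ICC of 0.05 (4 to 8 points for ICC 0.01 to 0.10), with 7 practices per arm and no balancing. Its effect on the result depends on prognostic strength, which the article does not give: 1.4 to 4.1 points for a 10-point gap over assumed odds ratios of 2 to 8. The power gain over the same range is about 0 to 4 points. The case for change rests on protection from imbalance and on the low cost, not on power.

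**What to change.** Under Statistical analysis, Primary outcome, name one prespecified multilevel logistic model with arm, age at start, gender and T0 white-spot status entered jointly, and take the effectiveness estimate from it.

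Define T0 status as any white spot on the scored teeth (yes/no), read by the blinded observers from the T0 photograph alone. State that the developmental-spot rule, which uses T1 and T2, does not revise it. T0 comes before appliance placement but after practice allocation, and the guideline includes measures before placement. The plan should therefore also say where T0 falls relative to those measures, so that the covariate can be treated as a baseline value.

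Keep the arm-only model as a sensitivity analysis and the one-by-one models as description. Do not use patients' opinion to adjust the effect.

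The cost is analysis wording, fixed before outcomes are seen, and one extra field at a reading already planned. There are no added patients, visits or readers. The odds ratio becomes conditional on the covariates. A patient without a readable T0 photograph lacks the covariate, but also lacks the reference needed to score the outcome.
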